## Abstract

**Background:**

Contemporary registry data indicate that only 20%–25% of patients following acute myocardial infarction achieve guideline-recommended low-density lipoprotein cholesterol (LDL-C) values <1.4 mmol/L (55 mg/dL). The present study aims to evaluate the impact of early intensive therapy (potent statin + ezetimibe ± bempedoic acid) on lipid control after myocardial infarction.

**Methods:**

This is a prospective, interventional, single-center study designed to assess the effectiveness of bempedoic acid in achieving LDL-C targets in patients following ST-elevation or non-ST-elevation myocardial infarction who remain insufficiently treated with atorvastatin plus ezetimibe. Patients not previously treated with lipid-lowering agents and presenting with admission LDL-C > 2.6 mmol/L (100 mg/dL) will be treated with atorvastatin (at least 40 mg/day or equivalent) plus ezetimibe (10 mg/day) for 6 weeks. Thereafter, the subgroup of patients failing to reach an LDL-C < 1.4 mmol/L (55 mg/dL) will be escalated to additive bempedoic acid (180 mg/day) for another 8 weeks. Those who reach the target will continue the aforementioned therapy. The primary endpoint is the proportion of patients who successfully achieve an LDL-C < 1.4 mmol/L (55 mg/dL) after 8 weeks of treatment with triple therapy. Secondary endpoints include the proportion of patients successfully reaching the target in the overall population and in the background medication group alone.

**Discussion:**

The results of this study will provide novel insights into post-infarction LDL-C control by evaluating the usefulness of an early intensive escalation oral lipid-lowering treatment strategy. Early intensive lipid-lowering triple oral therapy may facilitate the achievement of guideline-recommended LDL-C levels within the first 3 months after myocardial infarction compared with current clinical practice.

**Clinical Trial Registration:**

EudraCT 2022-003526-50

## Background

Low-density lipoprotein cholesterol (LDL-C) is one of the most important modifiable cardiovascular risk factors (1). In 2019, European guidelines lowered the recommended target LDL-C from <1.8 mmol/L (70 mg/dL) to <1.4 mmol/L (55 mg/dL) for secondary prevention in coronary artery disease (2). Despite well-intended recommendations and strong evidence, the previous LDL-C target of <1.8 mmol/L (70 mg/dL) had only been achieved in 21% in of patients included in registries (3, 4). In Germany, the reported proportion was even lower, with ≤15% of patients achieving the target following an acute coronary syndrome (5, 6).

After broader availability of more potent statins such as atorvastatin and rosuvastatin, we recently assessed the achievement of LDL-C guideline targets in real-world everyday clinical practice postmyocardial infarction. In brief, early standardized potent lipid-lowering therapy with atorvastatin plus ezetimibe resulted in nearly every second patient discharged after ST-elevation myocardial infarction (STEMI) achieving an LDL-C < 1.4 mmol/L (55 mg/dL) (7), with even higher rates in those receiving high-dose potent statins combined with ezetimibe (8).

In addition to high-intensity potent statins plus ezetimibe, proprotein convertase subtilisin/kexin type 9 (PCSK9) inhibitors such as evolocumab or alirocumab have shown additive clinical benefit in cardiovascular outcome trials (9, 10), but are not widely available for the overall population due to prescription limitations. In Germany, oral combination therapy must be escalated to the maximum level with documented inefficiency to reach the guideline-recommended LDL-C target prior to prescription of PCSK9 inhibitors. In the meantime, bempedoic acid has demonstrated a significant reduction in cardiovascular events when used as an oral add-on therapy in case of statin intolerance (11). Beyond that, adding bempedoic acid to maximally tolerated statins in high-cardiovascular-risk patients results in a further reduction of LDL-C by 17% (12). Therefore, bempedoic acid may offer a potential option to achieve guideline-recommended LDL-C targets <1.4 mmol/L (55 mg/dL) when standard combinations of a potent statin and ezetimibe are insufficient, and is currently required as part of stepwise escalation treatment prior to PCSK9 inhibition.

Several real-world registries document low achievement rates for guideline-recommended targets, with only one out of five patients reaching LDL-C < 1.4 mmol/L (55 mg/dL) (13, 14). However, recent prospective observations documented achievement rates of almost 50% with high-dose potent statin combined with ezetimibe (15), consistent with our own retrospective findings (7). Early combination of highly potent statin therapy with ezetimibe and bempedoic acid can further improve the response rate, as demonstrated in the LAI-REACT trial (16), though the ES-BempedACS trial showed no additional benefit (15). In that trial, however, one-third of patients were already receiving lipid-lowering therapy (15).

We planned and initiated the HAnnover ChOlesterol Lowering in Acute Coronary Syndrome (HACOL-ACS) trial to address three major clinically relevant questions: First, how many patients after a myocardial infarction reach the guideline-recommended target [LDL-C < 1.4 mmol/L (55 mg/dL)] on dual therapy with atorvastatin (at least 40 mg/day or equivalent) plus ezetimibe (10 mg/day)? Second, how many of the patients not achieving the target on a dual statin/ezetimibe therapy reach the target after adding bempedoic acid? Third, how many patients miss the target despite escalated oral triple lipid-lowering therapy and therefore need referral for PCSK9 inhibition? Our trial is distinct from the ES-BempedACS trial, as it focuses exclusively on patients without previous lipid-lowering therapy and will demonstrate the exact additive impact of bempedoic acid on top of dual therapy in each patient due to its sequential escalation strategy. Thereby, we will evaluate the real-world, guideline-mandated stepwise oral escalation therapy and quantify the residual unmet need for LDL-C target achievement. Starting with dual background medication is consistent with current guideline recommendations (17), and sequential add-on with bempedoic acid is also guideline-recommended (17), although this approach has never been tested in clinical practice. It is therefore important to document the efficacy of additive bempedoic acid on top of established and tolerated high-intensity statin treatment in combination with ezetimibe, to provide data supporting such recommendations. This is particularly important for the trial to be conducted in a sequential and clear manner as recent data from the ES-BempedACS trial with varying pretreatment populations did not show an additive LDL-C-lowering effect of bempedoic acid (15). Similarly, data from a recent oral PCSK9 inhibitor trial showed only a marginal additive effect in the bempedoic acid-treated comparator group when added to stable statin therapy (18).

The results of HACOL-ACS will also provide meaningful information for patients beyond the German healthcare system. While the trial design is adapted to national settings, the proportion of patients achieving guideline-recommended LDL-C targets at the end of the trial with double and triple therapies will be applicable both in regions with sequential dose escalations and in those allowing triple therapy from the beginning.

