**Figure 1 F1:**
[figure not shown]
Study algorithm. eGFR, estimated glomerular filtration rate; Hx, History of …; LDL-C, low-density lipoprotein-cholesterol; NSTEMI, Non-ST-segment myocardial infarction; STEMI, ST-segment myocardial infarction.

Group A will consist of the subgroup of patients who do not reach the LDL-C guideline target [LDL-C < 1.4 mmol/L (55 mg/dL)] after 6 weeks and will receive additive bempedoic acid (180 mg/day) for another 8 weeks (Triple therapy). Group B will consist of the subgroup of patients who achieve the LDL-C guideline target after 6 weeks of treatment with atorvastatin plus ezetimibe and who will continue on dual therapy for another 8 weeks (Dual therapy).

The 6-week escalation interval reflects local healthcare system, including certain reimbursement constraints, while aligning with evidence-based preferences to minimize delays in treatment intensification.

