#### Study intervention/treatment

After the index hospitalization and enrolment into the trial, standard medication including atorvastatin (40 mg/day) and ezetimibe (10 mg/day) will be recommended. After 6 weeks (Stage I), a study visit will be conducted at the institution and another lipid test will be performed. Next (Stage II), study medication (bempedoic acid, 180 mg/day, provided by Daiichi Sankyo, Munich, Germany) will be given at V2 to patients with LDL-C 1.4-2.8 mmol/L (55-110 mg/dL) (Group A), and patients with LDL-C < 1.4 mmol/L (55 mg/dL) will be continued on the background medication with the previous dosing (Group B). Patients with LDL-C > 2.8 mmol/L (110 mg/dL) at week 6 will be directly referred for PCSK9 inhibition outside the trial. Patients with LDL-C ≤ 2.8 mmol/L (110 mg/dL) mg/dL will have a revisit (V3) after another 8 weeks, including another lipid test.

The dose of bempedoic acid— 180 mg/day—will not be modified. The background medication is atorvastatin (40 mg/day) plus ezetimibe (10 mg/day), which is the standard discharge medication. If—despite explanation about the study protocol—patients are escalated by their treating physicians to higher doses of atorvastatin (>40 mg/day) or switched to rosuvastatin (minimum 20 mg/day), this will be considered stable baseline medication with regard to the study protocol. Switching between medications and de-escalation of statin treatment are strongly discouraged. A sensitivity analysis excluding patients with escalated doses of atorvastatin or switching to equal doses of rosuvastatin is planned.

Remaining study medication will be counted upon return at V3. Aside from adherence to lipid-lowering therapy, no other restrictions apply to routine care.

This strategy reflects current guideline recommendations to either initiate or escalate to a dual lipid-lowering therapy with a high-dose potent statin in combination with ezetimibe prior to adding a third compound (17). It also supports the generalizability of HACOL-ACS results to broader patient populations.

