#### Study endpoints

The primary endpoint is defined as the proportion of patients (%) in Group A who successfully achieve the European Society of Cardiology (ESC) LDL-C guideline target after Stage II. Secondary endpoints comprise the following: proportion of patients (%) who successfully achieve ESC LDL-C guideline targets [LDL-C < 1.4 mmol/L (55 mg/dL)] after treatment with dual therapy including atorvastatin (at least 40 mg/day or equivalent) plus ezetimibe (10 mg/day) at 6 and at 14 weeks; the proportion of patients (%) who successfully achieve the ESC LDL-C guideline targets after 14 weeks of treatment; the proportion of patients (%) who achieve American heart Association (AHA)/American College of Cardiology (ACC) guideline-recommended treatment targets of LDL-C < 1.8 mmol/L (70 mg/dL) after 14 weeks of treatment in the triple therapy group; mean change from baseline to week 6 and week 14 in LDL-C, total cholesterol, HDL-C, triglycerides, uric acid, creatine kinase, systolic and diastolic blood pressure, and heart rate; the proportion of non-compliant patients (%) taking less than 90% of the allocated study medication; and mean change from baseline to week 6 and to week 14 in quality of life.

Safety will be assessed by monitoring and recording all adverse events, serious adverse events, and certain laboratory parameters (further described under pharmacovigilance).

The primary endpoint was chosen to focus on the efficacy of the investigational compound in order to prevent that a higher than anticipated achievement rate of the LDL-C target on the baseline medication might result in an escalation subgroup being too small to conduct proper statistical analyses.

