## Limitations

The study has a single-center, open-label, non-randomized design, which introduces potential bias. For example, the single-arm design inherits the risk that changes in food intake, general lifestyle, and background medication over time may influence LDL-C and, thereby, the estimate of LDL-C-lowering effects of bempedoic acid. Hence, our study is exploratory regarding the escalation strategy and non-comparative.

HACOL-ACS is a short-term feasibility trial testing the applicability of sequential add-on bempedoic acid when guideline-recommended LDL-C targets are not achieved with tolerated high-intensity statin treatment combined with ezetimibe. The purpose of the trial is to describe the extent of additive LDL-C lowering provided by the sequential escalation. Given the small sample size and short duration, the trial does not assess long-term outcomes and, therefore, relies on surrogate endpoints, limiting clinical inference.

The single-center design and the fact that the study will be conducted within a specific healthcare system with defined prescribing constraints will impact but not prevent external validity and applicability to other settings. However, these prescribing constraints would have similar applicability even in a multicenter trial in a single country. The constraints on lipid-lowering therapy, however, allowed for prescription of atorvastatin, rosuvastatin, and ezetimibe, which will allow to use the most potent statins.

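### Group A is selected and judged on single LDL-C values against the same cut-off, so its responder rate cannot show the exact additive impact of bempedoic acid in each patient

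*Protocol article*

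**What the plan says.** Under Study design, "Group A will consist of the subgroup of patients who do not reach the LDL-C guideline target" after 6 weeks. Study intervention/treatment narrows this to a V2 LDL-C of 55-110 mg/dL; patients above 110 mg/dL leave for PCSK9 inhibition, and those below 55 mg/dL form Group B on unchanged dual therapy. The section describes one measurement at each end. At week 6, "a study visit will be conducted at the institution and another lipid test will be performed", and patients at or below 110 mg/dL "will have a revisit (V3) after another 8 weeks, including another lipid test".

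The primary endpoint is "the proportion of patients (%) in Group A who successfully achieve the European Society of Cardiology (ESC) LDL-C guideline target after Stage II", which is the same 55 mg/dL cut-off. The primary analysis is that proportion with an exact Clopper-Pearson interval (Statistical analysis).

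Two statements tie the result to the drug. The Background says that the trial "will demonstrate the exact additive impact of bempedoic acid on top of dual therapy in each patient due to its sequential escalation strategy". Study endpoints opens its justification with "The primary endpoint was chosen to focus on the efficacy of the investigational compound". The Limitations section calls the study exploratory and non-comparative and warns that "changes in food intake, general lifestyle, and background medication over time may influence LDL-C". It does not mention selection on a single value or regression to the mean.

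**The concern.** When patients are picked because one noisy value lies above a threshold, a second value tends to be lower even if nothing about the patient has changed. Those whose usual level is near 55 mg/dL will often cross it. In Group A this works towards apparent response, unlike diet, lifestyle or medication changes, which can act either way. Since every patient in the 55-110 mg/dL window receives bempedoic acid, no concurrent group shows how many would have crossed without it.

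What is at stake is how the primary rate is read. The Background contrasts this trial with one that found no added benefit of bempedoic acid, so attribution to the drug is part of its rationale. A rate read as drug effect would include crossings expected without drug, concentrated in the lowest of the four planned LDL-C bands.

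**Working it through.** **1. The plan's own figure.** For 30 responders of 60, the exact 95% Clopper-Pearson interval is 0.3681 to 0.6319, width 0.2639. The stated 26.4% is reproduced. This interval covers sampling error only and says nothing about the share of crossings that would occur without drug.

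**2. Inputs.**
- From the article: selection window 55-110 mg/dL; responder cut-off <55 mg/dL; about half of patients not at target at week 6 (Sample size), so a median week-6 LDL-C of about 55 mg/dL; 60 patients in Group A; anticipated responder rate 0.3-0.5; a 17% further LDL-C reduction with bempedoic acid (Background).
- Assumed, because the article does not give them: between-patient CV on treatment 25-40%; within-person CV 5-20%; log-normal values; independent within-person variation at V2 and V3; no drift; all V3 values observed.

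**3. Responders with no drug effect.** Simulation of V2/V3 pairs, 2 million patients per cell; entries are P(V3 < 55 | 55 ≤ V2 ≤ 110):

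| Between-patient CV | Within 5% | 8% | 10% | 15% | 20% |
|---|---|---|---|---|---|
| 25% | 9.0% | 14.1% | 17.3% | 24.2% | 30.0% |
| 30% | 7.7% | 12.2% | 15.0% | 21.4% | 27.2% |
| 40% | 6.3% | 10.0% | 12.4% | 18.2% | 23.4% |

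In patients, this runs from 60 × 0.063 ≈ 4 to 60 × 0.300 = 18.

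**4. Hand check of one cell.** With the cut-off at the median and no upper cap, P(V3 < 55 | V2 ≥ 55) = arccos(ρ)/π, where ρ = σ_b²/(σ_b² + σ_w²) and σ² = ln(1 + CV²). For CVs of 30% and 10%, σ_b² = 0.0862, σ_w² = 0.00995, ρ = 0.8965, and the probability is 0.146. The 110 mg/dL cap leaves 48.7% of patients in Group A, so the rate becomes 0.146 × 0.5 / 0.487 = 0.150, as in the table.

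**5. Where the crossings fall.** Across the grid, the no-drug rate is 13-40% in the 55-68.75 mg/dL band and 0-7% in the 96.25-110 mg/dL band.

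**6. With a true 17% reduction.** The observed Group A rate would be 40-57% across the grid. At CVs of 30% and 10% it is 47.9%, against 15.0% with no drug, so 47.9 − 15.0 = 32.9 points are attributable to the drug. The trial observes only the first of these three figures.

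**7. Per patient.** The difference of two single values has an SD of about 1.41 × the within-person CV, or about 14 percentage points at a CV of 10%. The expected effect is 17%, so a patient's own change does not isolate the drug's contribution.

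**8. Group B as a mirror image, and its limit.** On unchanged therapy, 6-29% of Group B would be at or above 55 mg/dL at V3 over the same grid. Without drift, crossings up and down balance in expectation, so subtracting Group B's losses from Group A's crossings (divided by n in A) would recover the attributable rate. With drift between V2 and V3 it does not. At log-SD 0.35, within-person CV 10% and a 17% effect:

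| Drift, both groups | Attributable rate | A-minus-B net rate |
|---|---|---|
| 5% down | 32% | 44% |
| none | 30% | 30% |
| 5% up | 26% | 15% |
| 10% up | 21% | about −1% |

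The errors are 11 to 22 points, against a no-drug crossing share of 13% in this scenario.

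**The case against.** The strongest reply is that the trial sets out to estimate a proportion and that the proportion is sound. The Background asks how many patients off target on dual therapy reach it after the add-on, and how many still need referral. The raw Group A rate answers both. The sentence justifying the endpoint goes on to explain that Group A was chosen so that the analysed subgroup would not become too small. All analyses are labelled descriptive, and the Limitations section concedes a single-arm, non-comparative design. All of this stands. A reader might infer that the primary endpoint or its analysis is faulty; the article does not support that.

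A reader might also infer that Group B's information goes unused. It does not: attainment on dual therapy at 6 and 14 weeks is a secondary endpoint, analysed by group with exact intervals. Everyone in Group B is below 55 mg/dL at V2, so loss of target is the complement of the planned week-14 rate among patients with an observed V3 value. The four LDL-C bands are planned too. Only the use of these figures as calibration would be new.

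The general caveat does not rescue the Background sentence. It contradicts that sentence without correcting it, and the influences it names are changes over time, whereas regression to the mean needs no change in the patient. Nor does the planned covariance analysis of A against B: it adjusts for the study-start value, while group is defined by the week-6 value and regression runs in opposite directions in the two groups.

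**Conclusion.** The point holds as one about what may be claimed. The design yields observed target attainment after escalation; it does not yield an exact additive effect of bempedoic acid, and least of all one for each patient. Without any drug effect, about 6-30% of Group A would be expected to count as responders, against an anticipated rate of 30-50%. That range rests on variabilities the article does not give and on no drift between V2 and V3. At the low end it is about 4 of 60 patients. Only the direction is certain.

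Two stronger readings go too far. One is that most of the observed rate would be artefact: the size cannot be fixed from the article, and under a true 17% reduction the drug accounts for the larger part in the example worked above. The other is that subtracting Group B's losses gives the true drug effect: this needs V2 and V3 to be exchangeable on unchanged therapy, and the Limitations section itself expects influences that could break that.

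**What to change.** 1. Replace the Background claim with wording such as *observed target attainment and LDL-C change after add-on, not corrected for regression to the mean*, and name regression to the mean under Limitations.
2. Beside the primary rate, and in each of the four V2 LDL-C bands, report the crossing rate expected with no drug effect over a stated range of within-person CV.
3. Show Group B's loss of target at V3 next to it as the mirror image, among patients with an observed V3 value. Counting missing values as losses would exaggerate it.
4. Do not present A minus B as a corrected drug effect. If it is shown at all, give it only as a sensitivity figure with a range of drift.

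The primary endpoint, its analysis and the sample size stay as they are. Recruitment is reported as running to March 2026, so these are changes of wording and reporting that use data already planned. The cost is a little extra descriptive analysis and a less favourable reading of the primary rate.

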## Methods/design

Reporting guidelines from Standard Protocol Items: Recommendations for Interventional Trials (SPIRIT) were used for this manuscript and table 2 (19). The HACOL-ACS trial is registered in the EudraCT database (Identification number: 2022-003526-50), which collects all items required by the World Health Organization Trial Registration Data Set. The trial has been approved by the local ethics committee at Hannover Medical School. Coordination is provided by the Center for Clinical Trials, including administrative tasks and data management. Patients undergo study-related procedures at the trial site (Department of Cardiology at Hannover Medical School, Germany). Statistic planning and evaluation are performed by the Institute of Biostatistics, and pharmacovigilance is overseen by the Department of Clinical Pharmacology.

### Study design

The study design according to protocol version 3.0 dated 13 November 2023, is depicted in Figure 1. This is a single-center, open-label, prospective, interventional study designed to precisely estimate the proportion of patients who successfully achieve LDL-C treatment targets as recommended by current guidelines. In Stage I, up to 135 patients will treated for 6 weeks with atorvastatin (at least 40 mg/day or equivalent) plus ezetimibe (10 mg/day). The chosen statin and its dose reflect the recommended regional background medication, established by consensus among local PCI hospitals, the regional Association of Statutory Health Insurance Physicians, and regional representatives for outpatient cardiologists. This consensus balances additive LDL-C-lowering efficacy against potential side effects (7). Thereafter, in Stage II, patients are split into two groups:

